**Methods and analysis:**

A single-blinded, 12-month follow-up, parallel-group cluster randomized controlled trial with a 1:1 allocation ratio will be implemented in two selected counties. In total, at least 2378 rural preschoolers aged 3–6 years old will be recruited from 12 preschools, 6 in Yang County and 6 in Shicheng County. Clusters will be randomized at the preschool level and allocated to the control group (routine school-based education) or the intervention group (routine school-based education plus the Safety Experience Room education). External support strategies will be implemented by local partners to minimize attrition. Data collection will be conducted at baseline and then every 3 months during a 12-month follow-up time period. Intention-to-treat (ITT) data analysis will be used. Generalized estimation equations (GEE) will evaluate the effectiveness of the program and generalized cost-effectiveness analysis (GCEA) will evaluate the cost-effectiveness of it. A per-protocol (PP) sensitivity analysis will assess the robustness of ITT results. Subgroup analyses will be performed to evaluate the impact of socio-demographic factors on the intervention effect, following the same strategies as the primary analyses.

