### Sample size

Based on a previous survey [28], we conservatively estimated that unintentional injury incidence among preschoolers aged 3–6 years old in the study sites over a 12-month period will be 30%. According to relevant reports [29], we estimated the effect size of the Safety Experience Room intervention will be 0.75 (incidence rate ratio) compared with a traditional educational intervention. An intra-class correlation (ICC) of 0.005 within a cluster size of 200 children per preschool was estimated [30, 31]. Nearly whole rural preschoolers stay enrolled in the same preschool throughout childhood, so we conservatively estimate a maximum attrition rate of 10% over the 12-month follow-up time period. Given these estimates, a minimum sample size of 2378 preschoolers is sufficient to achieve statistical power of 80% at the significance level of 0.05. Our preliminary surveys indicate most local rural preschools have 200 to 300 children, so 12 preschools will be adequate to recruit the needed sample size.

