**Fig. 2 Fig2:**
[figure not shown]
Timeline for participant enrollment, intervention implementation, and assessment

Each invited preschool will receive an official invitation letter along with relevant project materials. To avoid contamination between children within the same preschool, we will randomize the intervention and control programs at the school level. Consequently, 6 preschools will be randomly allocated to the intervention group, including 3 from Yang County and 3 from Shicheng County, while the other 6 preschools will be allocated to the control group, also including 3 from Yang County and 3 from Shicheng County.

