### Data analysis plan

Primary data analysis will employ an intention-to-treat (ITT) approach. Descriptive statistics will be calculated for socio-demographic variables and primary and secondary outcomes, including mean (or median) and standard deviation (or range and interquartile range) for continuous variables, and frequency and proportion for categorical variables. At each time point, Chi-square test and two-sample t-test (or Wilcoxon rank sum test if data are skewed) will be used to examine the differences in outcome measures between intervention and control groups for categorical and continuous variables, respectively. Trend tests or analysis of variance (ANOVA) will be used to detect within-group differences across the four follow-up visits.

We will also use Generalized Estimating Equation (GEE) and Generalized Linear Mixed Models (GLMM) to evaluate the overall effectiveness of the intervention after adjusting for socio-demographic variables, engagement, and baseline injury events. Both binary outcomes (whether experienced unintentional injury during the study period) and quantitative count outcomes (number of unintentional injury events and injury prevention knowledge score) at the individual level will be analyzed using these models. Zero-inflation models will be used when needed.

Missing values will be imputed using either the Expectation Maximization (EM) algorithm or Markov Chain Monte Carlo, as appropriate for the data. A per-protocol (PP) sensitivity analysis will be conducted to validate ITT results. All statistical analyses will be performed using the up-to-date version of R. All statistical tests will be two-sided, with the level of 0.05 considered statistically significant.

Subgroup analyses will be performed to assess the impact of socio-demographic factors on the intervention effectiveness, including sex and age of children, grade level of preschoolers, education level of preschooler caregivers, and household income per capita in the prior 12 months. Subgroup analyses will follow the same statistical strategies for primary analyses.

This study will be rigorously conducted, analyzed, and reported in accordance with the Standard Protocol Items: Recommendations for Interventional Trials (SPIRIT) 2013 statement [37] and the Consolidated Standards of Reporting Trials (CONSORT) 2010 statement [38].

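### GEE on 12 randomised preschools with no few-cluster method named: in its usual form it would reject a true null about 10–12% of the time, not 5%

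*Protocol article*

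**What the plan says.** The Preschool recruitment section makes the preschool the unit of allocation ("we will randomize the intervention and control programs at the school level") and fixes the numbers: "6 preschools will be randomly allocated to the intervention group, including 3 from Yang County and 3 from Shicheng County", with the mirror image in the control arm. The Sample size section says "so 12 preschools will be adequate to recruit the needed sample size" and claims "statistical power of 80% at the significance level of 0.05".

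The abstract gives the effectiveness method as GEE alone: "Generalized estimation equations (GEE) will evaluate the effectiveness of the program". The Data analysis plan adds a second model: "We will also use Generalized Estimating Equation (GEE) and Generalized Linear Mixed Models (GLMM) to evaluate the overall effectiveness of the intervention". It lists socio-demographic variables, engagement and baseline injury events as adjustment terms, and sets the error rate: "All statistical tests will be two-sided, with the level of 0.05 considered statistically significant". The software is R.

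The article does not give the GEE cluster variable, working correlation, variance estimator, reference distribution, degrees of freedom or any small-sample correction. It excludes none of them either.

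**The concern.** The robust (sandwich) variance of a GEE is justified as the number of clusters grows. With 12 clusters it is biased downward, because residuals from a fitted model are smaller than the true deviations. A normal reference also ignores that the variance rests on only 9 or 10 degrees of freedom. Both errors push towards rejection. More children per preschool does not help, because the number of clusters is what matters.

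The article therefore fixes a method, a cluster count and an error rate that do not fit together if the method is run in its ordinary form. The effectiveness result feeds the decision to offer the programme to control preschools and disseminate it across rural China, so a false-positive rate near twice the declared one would matter.

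**Working it through.** **Inputs from the article.** 12 preschools, 6 per arm, 3 per arm in each county; two-sided 0.05; 80% power; control incidence 30%; ratio 0.75, hence 22.5%; ICC 0.005; cluster size 200; attrition 10%.

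**Assumptions not in the article.** Beta-binomial clustering; coefficient of variation (CV) of cluster size between 0 and 0.4 (the stated 200–300 range suggests about 0.1); no adjustment beyond county.

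**1. The plan's own figure.** Unpooled two-proportion formula with normal quantiles:
- variance sum = 0.30×0.70 + 0.225×0.775 = 0.384375
- n per arm = (1.960 + 0.842)² × 0.384375 / 0.075² = 536.3
- design effect = 1 + 199×0.005 = 1.995
- total = 2 × 536.3 × 1.995 = 2140; divided by 0.90 = 2377.8, rounded up to 2378

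The stated 2378 is reproduced. The calculation uses normal quantiles and makes no allowance for having only 12 clusters.

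**2. Type I error of the usual GEE test.** With equal clusters and p cluster-level parameters, the uncorrected robust z equals a t statistic on 12−p df multiplied by √(12/(12−p)). Hence type I error = P(|t₁₂₋ₚ| > 1.96 × √((12−p)/12)).
- Arm only, p = 2: P(|t₁₀| > 1.789) = 10.4%
- Arm and county, p = 3: P(|t₉| > 1.697) = 12.4%

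Simulated checks:
- Arm only, 100,000 null trials per setting: 10.3–10.4% for equal clusters, 10.7–10.8% at size CV 0.2, 11.1–11.8% at CV 0.4. The result hardly changed for ICC between 0.001 and 0.05.
- 3,000 null trials fitted with an actual exchangeable logistic GEE: 10.1% arm only, 12.2% with county (Monte Carlo standard error about 0.6 points).

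**3. Interval length relative to the t-based interval.**
- Arm only: 1.789/2.228 = 0.80, about 20% too short
- With county: 1.697/2.262 = 0.75, about 25% too short

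**4. Effect of a county difference when county is omitted.** Allocation is balanced within county, so the arm contrast is free of the county difference while the arm-only variance absorbs it. At ICC 0.005 and 198 per preschool (200,000 null trials per setting):

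| County rate gap (points) | Type I error, arm only |
|---|---|
| 0 | 10.3% |
| 2 | 9.6% |
| 4 | 7.5% |
| 6 | 4.9% |
| 8 | 2.9% |

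The article gives no county rates, so the gap is an assumption.

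**5. What repairs it.**
- t reference alone on the uncorrected sandwich: P(|t₁₀| > 2.228×√(10/12)) = 6.9%, or P(|t₉| > 2.262×√(9/12)) = 8.2%. Not enough.
- Kauermann-Carroll variance with t₁₀, arm only: 4.8–5.0% for equal clusters, 5.2–5.7% at size CV 0.2–0.4. With county and equal clusters, each cluster has leverage 3/12, so the correction multiplies the variance by 12/9 and exactly undoes the bias in step 2.
- Mancl-DeRouen variance with t₁₀, arm only: 3.4–3.8%, conservative.

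**6. Power with a t reference.** SE = √(0.384375 × design effect / (6m)), where m is the number analysed per preschool; noncentrality = 0.075/SE.
- m = 178 (2378×0.90/12): design effect 1.885, SE 0.02605, noncentrality 2.88. Power is 82% with the normal reference and 74% with t₁₀.
- m = 198 (2378/12, no loss): design effect 1.985, SE 0.02534, noncentrality 2.96. Power is 84% with the normal reference and 76% with t₁₀.

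With t₉ the same noncentralities give about 73% and 75%.

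**The case against.** The strongest reply is that the article never says it will use an uncorrected sandwich with a normal reference. A reader might infer from the word GEE that the trial's error rate is about double the stated one. The documents do not support that. They are silent on variance estimator and reference distribution, and a statistical analysis plan or full protocol that is not shown may settle both. This stands, and it is why the point is conditional.

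Three further replies also stand:
- The GLMM is named beside GEE in the Data analysis plan, and all the figures here are for GEE. Nothing is shown about the GLMM's error rate.
- The 12% needs a county term, which the listed adjustment variables do not include. Without it, 10% is reached only if county rates are similar. One more cluster-level term would give P(|t₈| > 1.96×√(8/12)) = 14.8%, but the article lists no such term, so that figure should not be attached to this plan.
- Dissemination is tied to feasibility and economics as well as effectiveness, not to one p-value.

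These replies do not remove the point. The method, the 12 clusters and the 0.05 level are stated together, and the one inferential calculation on show uses normal theory. A corrected test written elsewhere would secure the error rate, but the stated 80% would not survive it at the planned size.

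**Conclusion.** The point holds in conditional form. GEE on 12 preschools, run with an uncorrected sandwich and a normal reference, has type I error of about 10% with arm alone and similar county rates, less if the counties differ and county is omitted, and about 12% with a county term. In the similar-rates and county-term cases its intervals are about 20% and 25% too short. The figures depend little on the ICC and rise modestly with unequal preschool sizes. They rest on beta-binomial clustering and on no covariates beyond county.

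If an unshown plan already specifies a few-cluster method, the sponsor can close the error-rate part by citing it. The power statement would still need revising: about 74–76% at the planned minimum on 10 df. Preschools larger than 200 would recover some of that, though less than proportionately because the design effect grows with cluster size.

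**What to change.** In the Data analysis plan, specify for the primary GEE analysis:
- preschool as the cluster;
- a county term, because allocation is balanced within county;
- a Kauermann-Carroll bias-corrected sandwich variance (Mancl-DeRouen is a conservative alternative, not an equivalent one);
- a t reference on 12 minus the number of cluster-level parameters: 10 with intercept and arm, 9 with county added.

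Both the variance correction and the t reference are needed. Add a cluster-level t test or a permutation test in support. A permutation test should follow the randomisation actually used: if six blocks of two are respected there are 2⁶ = 64 allocations, so the smallest two-sided p is 2/64 = 0.031.

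In the Sample size section, restate power with the t reference.

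The link function, the standing of the GLMM and the choice of child-level covariates are separate decisions that few-cluster bias does not settle.

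Cost: analysis wording and readily available software. The real price is wider intervals and power of roughly 74–76% (about 73–75% on 9 df) at 2378 children in 12 preschools. The sponsor must either accept this or offset it with more preschools.

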### Participant recruitment

All students attending participating preschools will be eligible to enroll in the study. Exclusion criteria include: (1) children who regularly attend preschools less than 3 full school days a week; (2) preschoolers who have mental or physical disabilities that prohibit valid participation in the learning activities of the Safety Experience Room; (3) preschoolers whose caregivers cannot cooperate with follow-up visits; and (4) preschoolers whose caregivers decline to sign informed consent.

In coordination with local governmental departments and agencies, we will recruit classroom teachers and school staff to help coordinate recruitment of study participants in each selected preschool. The teachers and staff members at each school will initially inform eligible preschoolers’ caregivers about the study via social media platforms (WeChat and QQ, the most popular applications in China), and then organize a caregiver-teacher meeting to communicate further about the study. Caregivers who agree to have their children participate in the study will be provided with an invitation letter that includes the benefits and responsibilities of participating in this study and be invited to read and sign an online informed consent.

Following consent processes, all participating caregivers will complete an online baseline survey to provide information on socio-demographic characteristics and details about unintentional injuries the children experienced in the prior 3 months, including the type and severity of each injury.

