### Randomization and masking

Once recruited, each enrolled preschool will be randomly allocated to a group by an independent (masked) researcher. Block randomization with a block size of 2 will be used to ensure balance between intervention and control groups. The allocation sequence will be generated by R version 4.0.4 software and the sequence will be sequentially numbered and opaque, stored in sealed envelopes until interventions are assigned. Group allocation will be concealed during data analysis.

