### Interventions

Both the intervention and control groups will receive routine school-based education on safety and injury prevention from their preschool. This education generally encompasses general health knowledge and skills, including injury prevention, and is performed by preschool teachers.

The intervention group will also receive the Safety Experience Room intervention. The Safety Experience Room involves creation of a space designed to teach safety and injury prevention. It can easily be renovated from typical Chinese preschool classrooms according to the standards in Table 1.

**Table 1 Tab1:** General description of the Safety Experience Room intervention design

Item	Requirement

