**II. General description and contents of the Safety Experience Room intervention**	
1. Target population	Preschoolers
2. Limit of participants	No more than 30 preschoolers at a time
3. Instructor	Preschool teachers or staff who receive standardized training
4. Guidance material	Operation Manual of the Safety Experience Room
5. Safety themes	
(a) Road traffic injury	(1) Learn basics of pedestrian traffic lights and zebra crossings – their appearances, functions, and purpose of usage (2) Never play around parked or moving vehicles or near roadways
(b) Falls	(3) Walk up and down stairs cautiously and do not climb on or near high indoor places such as tables, shelves, closets, cabinets, windows, or balconies (4) Never stand in puddles or on rocks, and do not climb high places outdoors without protection, such as trees, rocks, fences, or walls
(c) Drowning	(5) Seek adults for help when a person falls into the water (6) Swim only in places permitted by the government, with full-time adult supervision, and while wearing safety floats
6. Instructional materials	(1) Animation videos (2) Interactive games (teaching version) (3) Teaching props for simulations (4) Series of large-sized story books and the corresponding story recordings
7. Teaching activities	(1) Watching animation videos (2) Playing interactive games (teaching version) (3) Experiencing simulations of actual traffic and natural water environments (4) Reading story books and listening to story recordings (5) Summarizing key safety behaviors of the learning courses
8. Number of classes	Six 40-minute lessons, one weekly for six weeks. Each lesson has a single theme. Complete lessons are required to be implemented twice in a single semester.

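### The effectiveness models adjust for an undefined engagement variable that most naturally arises after allocation, so the arm coefficient may not be the effect of offering the programme

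*Protocol article*

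**What the plan says.** The Data analysis plan opens with the principle: "Primary data analysis will employ an intention-to-treat (ITT) approach". Its next paragraph says that GEE and GLMM will be used to "evaluate the overall effectiveness of the intervention after adjusting for socio-demographic variables, engagement, and baseline injury events", for the binary injury outcome, the injury count and the knowledge score. The abstract gives this model the central role: "Generalized estimation equations (GEE) will evaluate the effectiveness of the program". Subgroup analyses are to use the same strategy as the primary ones, so they inherit the same covariates.

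Engagement appears as a variable only in that one sentence, without definition, timing or instrument. Under Participant recruitment, caregivers "complete an online baseline survey to provide information on socio-demographic characteristics and details about unintentional injuries the children experienced in the prior 3 months"; engagement is not mentioned there. In the adjustment list, the word baseline attaches to injury events alone.

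On the programme itself, the Interventions section says: "The intervention group will also receive the Safety Experience Room intervention". Table 1 sets out "Six 40-minute lessons, one weekly for six weeks", with the full set delivered twice. Departures from protocol already have a place: "A per-protocol (PP) sensitivity analysis will be conducted to validate ITT results".

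**The concern.** An ITT comparison of arms stays unbiased under covariate adjustment when the covariates cannot have been changed by the allocation. Socio-demographic variables and prior injuries meet that condition. Engagement, on the natural reading, does not: the main thing described for a child to engage in is the Safety Experience Room, which begins after allocation and exists in one arm.

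Two cases follow if engagement is affected by allocation. If it is lesson uptake, controls score zero, and the arm coefficient becomes the contrast between controls and a hypothetical intervention child who attended nothing. If it is measured in both arms but raised by the programme, adjustment takes out whatever part of the effect runs through it. Either way the reported coefficient is not the effect of offering the programme, and the decision to disseminate the programme would rest on the wrong quantity.

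A lesser consequence holds only if engagement exists in one arm: the covariate would show the analyst which arm is which, although the plan says "Group allocation will be concealed during data analysis".

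**Working it through.** **Planned figure.** Inputs from the Sample size section: control risk 0.30, ratio 0.75 (so 0.225), two-sided 0.05, power 80%, ICC 0.005, cluster size 200, attrition 10%.

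- Per arm, unpooled: (1.960 + 0.842)² × (0.30 × 0.70 + 0.225 × 0.775) / 0.075² = 536.3.
- Design effect: 1 + 199 × 0.005 = 1.995.
- Total: 2 × 536.3 × 1.995 / 0.9 = 2377.8, so 2378. The stated size reproduces and is not at issue.

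**What the coefficient means.** Take log risk = b0 + b1·arm + b2·E, with E = 0 in controls. The arms differ on average by about b1 + b2 × (mean E in the intervention arm). That sum is the ITT effect; b1 alone is the contrast at E = 0. If the programme works wholly through E, b1 is near zero however well it works.

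**Simulation.** 400 trials per scenario; 6 + 6 preschools; 200 × 0.9 = 180 analysed children each; preschool SD on the risk scale √(0.005 × 0.30 × 0.70) = 0.032; log-link GEE with robust standard errors and the t critical value on 10 degrees of freedom (2.228). The true risk reduction averages 0.075, except in the null scenario. The models contain arm, with or without E, and no other covariates. The document gives no distribution for engagement, so these are assumptions:

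- A: uptake zero in controls, Beta(8.5, 1.5) with mean 0.85 in the intervention arm; reduction proportional to uptake.
- B: as A in structure, but uptake also depends on a child trait that lowers injury risk.
- B-null: as B, with no programme effect.
- C: engagement in both arms, related to that trait, unaffected by arm.
- D: engagement in both arms (mean 0.5 in controls, 0.7 in intervention, SD 0.15), carrying half the effect.

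| Scenario | RR without E | Rejects | SE of log RR | RR with E | Rejects | SE of log RR |
|---|---|---|---|---|---|---|
| A | 0.75 | 76% | 0.105 | 1.03 | 10% | 0.435 |
| B | 0.75 | 77% | 0.097 | 3.42 | 85%, wrong direction | 0.381 |
| B-null | 1.00 | 6.5% | 0.089 | 2.55 | 77%, false | 0.317 |
| C | 0.74 | 82% | 0.098 | 0.74 | 82% | 0.098 |
| D | 0.75 | 80% | 0.100 | 0.86 | 23% | 0.108 |

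The SE ratio in A is 0.435 / 0.105 = 4.1.

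**Hand check of D.** The slope on E is 0.0375 / 0.2 = 0.1875. At the midpoint E = 0.6, control risk is 0.30 − 0.1875 × 0.1 = 0.28125 and intervention risk is 0.28125 − 0.0375 = 0.24375. The ratio is 0.867, in line with the simulated 0.86.

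**Why B reverses.** Within the intervention arm, low uptake marks higher-risk children. Extrapolating to zero uptake attributes that excess risk to the arm.

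**The case against.** The strongest reply is that the term is undefined. This is a condensed article, and covariate definitions usually sit in the full protocol or SAP. A reader might infer that the plan knowingly conditions on a product of the intervention, and that the effect will be driven to null. The document supports neither as fact. The timing is an inference, and bias toward the null is only one of the outcomes above.

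Nor must a measure taken in both arms be affected by allocation. Both arms have the same quarterly caregiver meetings and surveys and the same evaluation games at matching times. Engagement built on these could respond to allocation but need not. Scenario C represents the harmless case.

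It can also be said that ITT governs which children are analysed and in which arm, and that a covariate does not change this. That is right: the fault lies in what the coefficient estimates, not in the analysis population.

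These points limit the claim without removing it. Engagement is absent from the listed baseline data, and the lessons follow allocation, so the post-allocation reading remains the natural one. The other between-arm tests in the plan do not replace the model: they are per time point, and the chi-square, t and Wilcoxon tests named there do not account for clustering by preschool.

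**Conclusion.** The point holds conditionally and should be settled before analysis. If engagement is affected by allocation, as the text most naturally implies, the planned models do not estimate the effect of offering the programme. With a true RR of about 0.75, the adjusted RR lies between 0.86 (power 23%) and 1.03 (rejection 10%) in the two scenarios without confounding. If uptake is also prognostic, it can reverse to 3.4, or reject a true null in 77% of trials. If allocation does not affect engagement, the estimate stays at 0.74 with 82% power.

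These sizes rest on assumed engagement distributions and show the range of possible harm; they do not forecast this trial's result. The masking consequence is secondary and applies only if engagement exists in one arm.

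**What to change.** Remove engagement from the adjustment set of every ITT GEE and GLMM, including the subgroup models, unless it is a measure fixed before allocation and the plan states this. Adjust only for pre-allocation variables, that is, socio-demographic characteristics and baseline injury events. Define engagement, say when and in which arm it is measured, and use it only in a labelled per-protocol, dose-response or complier analysis.

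The cost is a short text change in the analysis plan, with no added data collection and no change to the sample size.

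### Allocation is balanced within county, but county is not named among the model adjusters, so a county difference in injury risk would inflate the SE and cost power

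*Protocol article*

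**What the plan says.** Protocol article, Preschool recruitment: "6 preschools will be randomly allocated to the intervention group, including 3 from Yang County and 3 from Shicheng County". The control arm is made up the same way, so each county holds three preschools per arm. Study design places the two counties in different provinces. Randomization and masking mentions blocks of two and does not use the word stratified, but three blocks of two within each county would produce this 3+3 split.

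Protocol article, Data analysis plan: the effect is to be estimated by GEE and GLMM, "adjusting for socio-demographic variables, engagement, and baseline injury events". County does not appear there or elsewhere in that section. The socio-demographic factors spelled out for the subgroup analyses are sex, age, grade, caregiver education and household income.

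Protocol article, Sample size: "An intra-class correlation (ICC) of 0.005 within a cluster size of 200 children per preschool was estimated". The calculation uses one incidence for both study sites and has no county term.

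**The concern.** When allocation is forced to balance on a factor, the difference between arms no longer varies with that factor. The variance estimate benefits only if the analysis also removes the factor. If county is left out of a model clustered on preschool, the six preschools in an arm come from two populations with possibly different risks. The spread between those populations is then read as random variation between preschools. The SE is overstated, the interval is too wide and the type I error falls below its nominal level.

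What is at stake is power, in a trial with 12 randomised units. A real effect could be missed because of variation that the design had already controlled.

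**Working it through.** **Inputs from the documents.** Control incidence 30% and ratio 0.75, hence 22.5% in the intervention arm; ICC 0.005 with 200 children per preschool; 10% attrition; 80% power (all Sample size); two-sided 0.05 (Data analysis plan); 12 preschools, three per arm in each county (Preschool recruitment).

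**Assumption, not in the documents.** The control-arm gap between counties, taken as 0 to 10 percentage points and centred on 30%. The ratio of 0.75 is applied in both counties.

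**1. The plan's own figure.** With unpooled variance, n per arm = (1.960 + 0.842)² × (0.30×0.70 + 0.225×0.775) / 0.075² = 536.34. The design effect is 1 + 199 × 0.005 = 1.995. Total = 2 × 536.34 × 1.995 / 0.9 = 2377.8, rounded up to 2378. This matches the stated number. Analysed children per preschool: 2378 × 0.9 / 12 = 178.

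**2. How much variance a county gap adds.** Expressed as an ICC, the addition is (half the gap)² / (0.3 × 0.7).
- 5 points: 0.025² / 0.21 = 0.003
- 10 points: 0.05² / 0.21 = 0.012

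The planned ICC is 0.005.

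**3. Effect on the SE at a 10-point gap** (control 35% and 25%, intervention 26.25% and 18.75%).
- Within-county variance of a preschool proportion = p(1−p) × (1 + 177 × 0.005) / 178. Averaged over counties and summed over the two arms: (0.2075 + 0.1730) × 1.885 / 178 = 0.00403.
- True SE of the risk difference = √(0.00403 / 6) = 0.026.
- County spread in the sample variance of six preschools split 3/3 is 6/5 × (half the gap)². Summed over arms: 1.2 × (0.05² + 0.0375²) = 0.00469.
- SE as estimated without county = √((0.00403 + 0.00469) / 6) = 0.038.

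**4. Power and type I error.** Beta-binomial simulation, 178 children per preschool, within-county ICC 0.005. Cluster-level t test with 10 df without county and 9 df with county; at least 40,000 runs per setting.

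| Control-arm gap | Power without county | Power with county | Type I error without county |
|---|---|---|---|
| 0 | 74% | 73% | 5.0% |
| 2 points | 72% | 72% | 4.5% |
| 5 points | 64% | 73% | 2.6% |
| 10 points | 39% | 73% | 0.4% |

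With county in the model, the type I error stays at about 5%.

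**5. If 0.005 is the total ICC.** A gap of 2 × √(0.005 × 0.21) = 6.5 points would use up the whole planned ICC. At 5 points, the within-county ICC is 0.005 − 0.003 = 0.002. Power is then about 76 to 77% without county and 85 to 86% with it.

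**6. Check in an individual-level model.** Logistic GEE clustered on preschool and adjusted for each child's baseline injury, 300 runs per setting (simulation error up to about 3 points per figure). With bias-reduced SE and a t reference, power without county was 71%, 61%, 34% and 8% at gaps of 0, 5, 10 and 15 points, against 66%, 65%, 66% and 61% with county. Adjusting for individual baseline injury does not remove the county variance.

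**The case against.** **The adjuster list is in broad categories.** County of residence could be read as a socio-demographic variable, the itemised list belongs to the subgroup analyses, and an article may leave the full covariate list to another document. It is right that no sentence excludes county, and a reader should not infer a deliberate omission. But the article does state an adjustment set, and the one factor on which it fixes the balance is not named there. Naming it is a concrete improvement.

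**A reader might infer that any county difference destroys the power.** It does not: at 2 points the loss is negligible, and only moderate or large gaps matter. The documents give no gap. A harsher 62% and 32% at 5 and 10 points arise if the same absolute gap is assumed in both arms. At 10 points that implies ratios of 27.5/35 = 0.79 and 17.5/25 = 0.70, whereas the plan has a single ratio of 0.75.

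**A reader might infer that 0.005 is credible only as a within-county ICC.** Sample size does not say which kind it is, and the sources it cites are not at hand. If it is a total ICC, a 5-point gap is already in the planned variance (step 5).

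**A reader might infer bias.** The 3+3 split protects the estimate from county confounding, and the error is conservative.

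**The simulation is not the planned model.** This stands in part. Income and caregiver education may carry some of a county difference and were not simulated. With plain robust SEs, the GEE check gave 83% without county at 5 points, above the planned 80%. However, the cluster-level equivalent of that test, with a z reference, had a type I error of about 10 to 12% when the counties did not differ. Also, the 73 to 74% with no gap comes from having 12 clusters and is a separate matter.

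**Conclusion.** The point holds as a recommendation to name county in the model. It does not show that the trial is biased or certain to be underpowered. Under the assumptions in step 4, leaving county out costs almost nothing at a 2-point gap, about 9 points of power at 5 points (64% v 73%) and about 34 at 10 points (39% v 73%). If the planned ICC already contains county variation, including county at a 5-point gap adds about 9 points to a power no lower than that with no gap.

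This rests on three conditions: the analysis clusters on preschool, a unit that Data analysis plan does not name; the ratio is the same in both counties; and the other covariates do not absorb the county difference.

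**What to change.** In Data analysis plan, name county as a fixed effect in the primary GEE/GLMM and in the supporting models. Count it in any small-sample reference distribution (12 − 3 = 9 df). Restrict any permutation test to re-allocation within county, and within the blocks of two if these were formed inside county. It would also help to say in Sample size whether the ICC of 0.005 is within county or total.

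County is known for every preschool, so no data need be collected. The cost is one degree of freedom: about 1 point of power in the cluster-level test when the counties do not differ (74% v 73%). With a bias-reduced GEE it may be somewhat more: the 300-run check gave 71% v 66% at no gap.
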